## Abstract

**Background:**

The construction of a colostomy is a common procedure, but the evidence for the different parts of the construction of the colostomy is lacking. Parastomal hernia is a common complication of colostomy formation. The aim of this study is to standardise the colostomy formation and to compare three types of colostomy formation (one including a mesh) regarding the development of parastomal hernia.

**Methods/Design:**

Stoma-Const is a Scandinavian randomised trial comparing three types of colostomy formation. The primary endpoint is parastomal herniation as shown by clinical examination or CT scan within one year. Secondary endpoints are re-admission rate, postoperative complications (classified according to Clavien-Dindo), stoma-related complications (registered in the case record form at stoma care nurse follow-up), total length of hospital stay during 12 months, health-related quality of life and health economic analysis as well as re-operation rate and mortality within 30 days and 12 months of primary surgery. Follow-up is scheduled at 4-6 weeks, and 6 and 12 months. Inclusion is set at 240 patients.

**Discussion:**

Parastomal hernia is a common complication after colostomy formation. Several studies have been performed with the aim to reduce the rate of this complication. However, none are fully conclusive and data on quality of life and health economy are lacking. The aim of this study is to develop new standardised techniques for colostomy formation and evaluate this with patient reported outcomes as well as clinical and radiological assessment.

**Trial registration:**

Clinicaltrials.gov, NCT01694238.2012-09-24.

## Background

Colostomy formation has been a standard surgical procedure for more than 100 years. A well-functioning colostomy may not negatively affect the patient’s quality of life (QoL) [1]; however, this can only be said if the stoma is well functioning and if complications are kept to a minimum. The complication rates after stoma formation are considerable, with figures of 21-70% [2,3], and studies have shown that adequate stoma height, type of stoma, body mass index (BMI), emergency surgery and gender may be of importance in reducing the risk of complications in both the short- and long-term perspectives [4-6].

The surgical technique of stoma formation is only partly evidence based. There are few studies focused on technical details about stoma construction and their future impact on stoma function. One study has attempted to standardise the skin incision to two-thirds of the width of the bowel [7], although the actual impact of this on the functional outcome of the stoma function was not presented. In the surgical literature a cruciate incision in the fascia and extraction of the bowel through a hole sufficient in size is a standard description of the surgical technique [8]. In clinical practice the sufficient size of the hole has often been equal to ‘two fingers-width’ , which is a fairly inexact measurement.

Parastomal hernia is a long-term complication that is common; in the literature figures up to almost 50% have been reported [9,10]. There have been discussions regarding the placement of the stoma and effects on hernia incidence [11,12]; however, no studies have been sufficient in design or size to thoroughly answer the question. Attempts to reduce the rates of parastomal hernias have been made in the last few years with the placement of a mesh at the construction of the stoma [13-18]. However, these trials did not include studies of health-related QoL or health economic aspects. The placement of a prophylactic parastomal mesh has not been universally accepted, mainly due to a hesitance related to the possible risk of infection with a foreign body, but also as most studies were small in sample size [19]. Another suggestion for the basic construction of the stoma has been to make a circular instead of a cruciate incision in the fascia, but this has not been studied. It has been described in conjunction with the use of circular stapling devices, and no hernias were found, but the studies were small [20,21]. Thus, it is apparent that further studies are desired [17,22-24] and several randomised controlled trials are registered and ongoing.

The evaluation of parastomal hernias can be performed by clinical examination, CT scan or ultrasound [14,15,25,26]. All techniques have advantages and disadvantages, and the conclusion must be that evaluation of parastomal hernias may be difficult and must be standardised in a study.

The hypothesis to be tested in this study is that it is possible to obtain a lower incidence of parastomal hernia with a circular incision in the abdominal fascia or with reinforcement with a mesh instead of a cruciate incision in the abdominal fascia.

The study will provide a precise control compared to the two interventions with thorough measurements of the bowel and the trephine opening to improve the evaluation of the surgical technique. It will also enable an evaluation of QoL and health economy.

## Methods

### Study objective

The Stoma-Const trial is a randomised trial comparing three different surgical procedures for the construction of a colostomy.

### Endpoints

The primary endpoint is the presence of parastomal hernia as detected by clinical examination or CT scan at 12 months after surgery. A bulge in the vicinity of the stoma is not sufficient in this study to define a parastomal hernia. If there is any doubt in the clinical setting, the patients must be examined by a CT scan in a prone position. Secondary endpoints include: re-admission rate, postoperative complications (classified according to Clavien-Dindo [27]), stoma-related complications (registered in the case record form (CRF) at Stoma Care nurse follow-up), total length of hospital stay during 12 months, health-related quality of life and health economic analysis, re-operation rate, mortality within 30 days and 12 months of primary surgery. Re-admissions and re-operations as registered in the hospitals’ databases at 24 months to ascertain that possible long-term complications related to the stoma construction are identified.

### Inclusion criteria

Patients are eligible if the following conditions are met:

•the patient is presenting with a condition for which an elective surgical procedure is planned including formation of a colostomy

•it is possible to operate on the patient in regard to concomitant disease

•the patient has given informed consent to participate

### Exclusion criteria

•Participation in other randomised trials in conflict with the protocol and endpoints of the Stoma-Const trial.

### External validity

All patients with a condition for which an elective surgical procedure is planned including a colostomy formation, and who are not included and randomised, will be registered in the ‘screening log’ at each participating centre including information on date, hospital, gender, age, ASA classification and type of operation. The reason for non-inclusion or exclusion is noted.

### Randomisation

All participating patients give written informed consent. After inclusion no changes are made in the planning for the operation. The patient will be randomised to one of the three groups of intervention during surgery in the operating theatre directly prior to the stoma formation (Figure 1). Randomisation will be performed by blocks of closed envelope systems in each participating hospital. It will be balanced and stratified by hospital. Laparoscopic as well as open procedures will be included and, although not stratified by open or laparoscopic procedures, their use will be noted in the CRF.

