**Figure 1 F1:**
[figure not shown]
Consort diagram for the Stoma-Const trial.

Including hospitals may choose to randomise between all three techniques or two of them. This decision is made before the hospital enters the study. The blocks will be set up according to this system, and the total number of 80 patients in each group will be managed through this system.

When patients are not subject to the treatment modality as randomised, data will be analysed on an ‘intention-to-treat basis’ (once randomised, patients will not be excluded or change groups because of conversion or type of surgery). Patients who do not consent to participation or are excluded will be treated by cross incision in the fascia as the usual routine.

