### Follow-up

The follow-up during the postoperative hospital stay is recorded in a CRF. Time until full oral feeding is resumed and time until first gas and stool are registered.

Patients will be clinically examined at 6 (5–7) months and at 12 (11–13) months postoperatively and further as needed (suspected parastomal herniation), by a surgeon (not one of the colorectal team) preferably specialised in hernia surgery, to diagnose a possible parastomal hernia. At 12 months patients for whom no clinical parastomal herniation has been found will undergo a CT examination of the abdomen (wall), performed in prone position [25], which also will be part of the routine 12 months follow-up by abdomen CT for colorectal cancer patients. A study-specific standardised referral to abdomen CT is used, and although the study is not blinded, no information as to type of stoma construction is included. All radiologic departments use a specific protocol for this part of the abdomen CT.

Stoma height, diameter, colour, skin irritation and bandaging problems are documented by nurses specialised in stoma care during hospitalisation and at 4-6 weeks, 6 months and 12 months and are registered in a CRF.

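### Blocked envelopes within each hospital, in an unblinded trial that randomises in theatre after consent, leave an opening for selection before allocation

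*Protocol article*

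**What the plan says.** All references are to the protocol article.

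- **Method (Randomisation).** "Randomisation will be performed by blocks of closed envelope systems in each participating hospital", and "It will be balanced and stratified by hospital".
- **Timing (Randomisation).** Consent comes first. The patient is randomised later, "during surgery in the operating theatre directly prior to the stoma formation".
- **Number of arms (Randomisation, text after Figure 1).** "Including hospitals may choose to randomise between all three techniques or two of them". The hospital decides before it enters, and "The blocks will be set up according to this system". No block length is given.
- **Blinding (Follow-up).** The CT referral hides the technique: "although the study is not blinded, no information as to type of stoma construction is included". The operating team necessarily knows which technique each of its patients received.
- **Where the intention-to-treat rule starts (Randomisation, text after Figure 1).** "once randomised, patients will not be excluded or change groups because of conversion or type of surgery".
- **Patients outside the trial (same place).** "Patients who do not consent to participation or are excluded will be treated by cross incision in the fascia as the usual routine". That is the control technique.
- **Screening log (External validity).** Eligible patients who are not included and randomised are logged at each centre with date, hospital, gender, age, ASA class, type of operation and the reason.

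**The concern.** Each feature is defensible alone; the difficulty lies in the combination. Blocks within a hospital tie the next allocation to the ones before it. The team knows those earlier allocations because the study is open. Randomisation happens in theatre, so between consent and allocation there is an interval in which a team that can foresee the next arm could decline to randomise the patient.

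Such a patient never enters the full analysis set, which is built from randomised patients, so intention-to-treat analysis cannot repair the resulting imbalance. The team knows BMI and immunosuppression before allocation. The Background cites BMI as relevant to stoma complications, and the Statistical analysis section plans subgroups on both. If high-risk patients were left out more often when one particular arm was expected, that arm would look better than it is.

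**Working it through.** **Plan's own figure, used only for scale.** The Statistical analysis section assumes 30% against 10%, two-sided 5%, 80% power, and gives 62 per group. With the usual chi-square formula, n = [1.960·√(2·0.20·0.80) + 0.842·√(0.30·0.70 + 0.10·0.90)]² / 0.20² = (1.109 + 0.461)² / 0.04 ≈ 61.6, so 62. It reproduces, and nothing below changes it. The planned difference is 20 percentage points.

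**Assumptions for predictability, because the article gives no block size.** Blocks have a fixed length that the team knows or infers, with equal allocation, k arms and m places per arm (block length k·m). The team knows all earlier allocations in the block.

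**Share of allocations known with certainty.** The next arm is certain when only one arm has places left. A given place comes after all (k − 1)·m places of the other arms with probability 1/((k − 1)·m + 1). Averaged over the block, the certain share is therefore 1/(m + 1) for two arms and 1/(2m + 1) for three.

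| Places per arm (m) | Two arms: block, certain, best guess | Three arms: block, certain, best guess |
|---|---|---|
| 1 | 2, 50%, 75% | 3, 33%, 61% |
| 2 | 4, 33%, 71% | 6, 20%, 56% |
| 3 | 6, 25%, 68% | 9, 14%, 53% |
| 4 | 8, 20%, 67% | 12, 11%, 51% |
| 5 | 10, 17%, 65% | 15, 9%, 50% |

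The best guess names the arm with most places left. For a two-arm block of 4 it is right (1/2 + 2/3 + 2/3 + 1)/4 = 70.8% of the time, against 50% by chance. For a three-arm block of 3 it is (1/3 + 1/2 + 1)/3 = 61.1%, against 33%.

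**What selection could do to the result (illustration only; none of these inputs is in the article).** Suppose no treatment effect, a 20% hernia rate overall, and 30% of patients at high risk with a 40% rate. Low-risk patients then have (0.20 − 0.30·0.40)/0.70 = 11.4%. Suppose also that a high-risk patient is left unrandomised whenever the control arm is already exhausted in the block. An experimental place falls after all m control places with probability 1/(m + 1), whether there are two arms or three.

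- *Always done.* The experimental rate is 20 − (20 − 11.4)/(m + 1). With m = 2 (two-arm block of 4, three-arm block of 6) it is 17.1%; with m = 1 (three-arm block of 3) it is 15.7%. Control stays at 20%, so the spurious difference is about 3 to 4 points.
- *Done half the time.* The high-risk share at those places is 0.15/(0.70 + 0.15) = 17.6%, and their rate is 0.176·40 + 0.824·11.4 = 16.5%. The spurious difference is 3.5/3 = 1.2 or 3.5/2 = 1.8 points.

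A simulation of the same scenario agreed (control about 20% against 17% or 16% when always done). The direction follows from the assumed habit. A team that skipped high-risk patients when an experimental arm was ruled out would bias the other way.

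**The case against.** The strongest reply is that predictability depends on details a journal article leaves to the full protocol. The article says only that blocks are used. It does not say that their length is fixed or disclosed, and withholding the length during recruitment helps concealment. Opaque, numbered envelopes held by an independent person may be specified elsewhere. This stands: the percentages are conditional, and silence on opacity, numbering and custody is not a finding. What remains is the method the article does state, for which a stronger and cheap alternative exists.

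It is also fair that randomising immediately before stoma formation limits losses after randomisation, that the screening log makes selective omission partly visible, and that the illustrated bias is small beside 20 points.

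A reader might infer more than the text supports:

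- *That staff may discard an envelope and open another.* No section describes or permits this. That the envelopes are physically kept at the hospital is the natural reading, but it is not said outright.
- *That surgeons have discretion to drop a consented patient.* The cross-incision sentence concerns patients who do not consent or are excluded, and the only exclusion criterion is a conflicting trial. The interval exists, but the article does not license its use.
- *That the decision could rest on measured bowel calibre or a contaminated field.* The Surgical procedure section places randomisation before the colon is measured. Contamination is nowhere mentioned, and only elective surgery is eligible.
- *That two-arm hospitals are easier to foresee.* Gain over chance is 21 points (block of 4) or 18 (block of 6) with two arms, but 28 (block of 3) or 23 (block of 6) with three.
- *That participating surgeons are reluctant to use mesh.* The Background reports hesitance in general, and a hospital may choose two techniques without mesh.

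**Conclusion.** The point holds as a weakness in a stated design choice. Per-hospital envelope blocks, an unblinded study, allocation in theatre after consent, and an intention-to-treat rule that begins at randomisation together leave an opening for selection bias. If a fixed block length is known or inferred, the next arm is certain for about 17% to 50% of allocations with two arms (blocks of 10 down to 2) and 9% to 33% with three (blocks of 15 down to 3). These block sizes are assumed.

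The article does not show that selection occurred, and that should not be inferred. Under the illustrative assumptions, the spurious difference would be 1 to 4 points. The screening log helps afterwards but prevents nothing. Because it lists neither BMI nor immunosuppression, selection on those factors would be hard to see. The point is worth acting on because the article reports that recruitment continues and imbalance of this kind cannot be removed at analysis.

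**What to change.** For the remaining recruitment, replace the hospital envelopes with web or telephone allocation run from the trial coordinating centre. Keep stratification by hospital and each hospital's choice of two or three arms. Use randomly varying block sizes concealed from sites, and release the arm only after the patient's trial number has been irrevocably registered in theatre. Report consented but unrandomised patients by hospital, with reasons; recording their BMI as well would make the screening log more informative.

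If envelopes must stay, state that they are opaque and sequentially numbered with varying block sizes, have the trial number and time written on each before opening, and reconcile used envelopes centrally against the consent list.

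Varying blocks remove most of the certainty but not all guessing, since the running tally at a hospital still gives some guide. That is why the count of unrandomised patients is needed in either case. The cost is a small set-up and one call or log-in from theatre per patient. The sample size does not change.

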**Figure 1 F1:**
[figure not shown]
Consort diagram for the Stoma-Const trial.

Including hospitals may choose to randomise between all three techniques or two of them. This decision is made before the hospital enters the study. The blocks will be set up according to this system, and the total number of 80 patients in each group will be managed through this system.

When patients are not subject to the treatment modality as randomised, data will be analysed on an ‘intention-to-treat basis’ (once randomised, patients will not be excluded or change groups because of conversion or type of surgery). Patients who do not consent to participation or are excluded will be treated by cross incision in the fascia as the usual routine.

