### Statistical analysis

The Swedish trial on the effect of prophylactic net placement has reported 50% incidence of parastomal hernia without mesh [14]. Our own data on abdominoperineal excision from Sahlgrenska University Hospital indicate an incidence of 25% [28]. The power calculation based on available information has used the hypothesis that the cruciate incisional stoma formation, performed as described here, should result in parastomal hernia incidence of 30% and the circular incision or prophylactic mesh reinforcement could reduce this incidence to 10% each. An 80% power and a 5% level of significance with a two-sided alternative hypothesis would require 62 patients per group using a chi-square test. Expecting 20% drop-outs, 80 patients will be recruited in each group.

The primary analysis will be based on the full analysis set. This analysis set is designed to be consistent with recommendations set forth in International Conference on Harmonisation (ICH) guidance document E9: Statistical Principles for Clinical Trials, and is intended to adhere as closely as practically possible to the intention-to-treat (ITT) principle. The full analysis set will consist of all randomised patients who had surgery and who contributed with any follow-up data.

Patients will be analysed according to randomised procedure. A sensitivity analysis evaluating the actual procedure will be made for the most important outcomes.

All hypothesis testing will be conducted using two-sided tests, and P values ≤ 0.05 after rounding will be considered statistically significant. A pair-wise comparison between the experimental arms and the control arm will be performed and the significance level will be corrected using the Bonferroni-Holm method. Event-type variables (yes or no) will be compared between randomised procedures using chi-square tests, and relative risks and risk differences will be estimated. Where appropriate, the time to event will be described using Kaplan-Meier plots. The number of events of a certain type (for example, number of complications or re-operations) will be analysed using Poisson regression with randomised procedure as a factor and time under observation as an offset variable.

Total length of hospital stay will be compared between groups using Wilcoxon’s rank-sum test. Sub-group analyses specifically looking at the following groups of patients will be performed:

a) BMI >30 kg/m2

b) Immunosuppression

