Sensitivity analyses will be performed for the primary variable and selected secondary variables, as deemed appropriate, where groups are compared pair-wise utilising only data from centres where both treatments were allocated.

Exploratory analyses (such as logistic regression) may be performed to investigate the influence of background factors (patient characteristics, perioperative factors) on outcomes.

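### The primary comparison pools patients from hospitals that did not offer one of the compared arms, while the comparison within hospitals that randomised both is only a sensitivity analysis

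*Protocol article*

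**What the plan says.** All of this is in the protocol article, under Methods.

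- **Arms on offer (Randomisation, text after Figure 1).** "Including hospitals may choose to randomise between all three techniques or two of them". "This decision is made before the hospital enters the study". No pair is excluded, so a hospital could randomise circular against mesh with no cruciate control.
- **Randomisation.** Closed envelopes in blocks at each hospital: "It will be balanced and stratified by hospital". On arm totals: "the total number of 80 patients in each group will be managed through this system".
- **Primary population (Statistical analysis).** "The full analysis set will consist of all randomised patients who had surgery and who contributed with any follow-up data". There is no limit by centre.
- **Primary test (Statistical analysis).** "A pair-wise comparison between the experimental arms and the control arm will be performed", with Bonferroni-Holm correction. "Event-type variables (yes or no) will be compared between randomised procedures using chi-square tests, and relative risks and risk differences will be estimated".
- **Same-centre comparison (end of Statistical analysis).** A sensitivity analysis in which "groups are compared pair-wise utilising only data from centres where both treatments were allocated", for the primary variable and selected secondary variables.

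**The concern.** Randomisation protects a comparison of two arms only among patients who could have been allocated to either. Take cruciate versus circular. A patient at a cruciate/mesh hospital could not receive a circular incision but counts as a control for it. A patient at a circular/mesh hospital is compared with cruciate patients treated elsewhere. Which arms a hospital offers is its own choice, so this part of the primary contrast is a comparison between self-selected hospitals.

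Hospitals can differ in case mix, surgeons, postoperative care (left to local guidelines) and detection. Under Follow-up the study is unblinded and the examining surgeon is only preferably a hernia specialist. If such differences go with the choice of arms, they enter the primary risk difference as bias, and the test may reject too often when there is no effect. The comparison free of this problem does not carry the primary conclusion.

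**Working it through.** **1. The plan's own figure.** Inputs from Statistical analysis: 30% versus 10%, two-sided 5%, 80% power, chi-square test.

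n = [1.960·√(2·0.20·0.80) + 0.842·√(0.30·0.70 + 0.10·0.90)]² / 0.20² = (1.109 + 0.461)² / 0.04 ≈ 61.6, so 62 per group. This reproduces the plan. Allowing for 20% drop-out, 62/0.8 = 77.5, so 78; the plan recruits 80, which leaves 64 evaluable per arm.

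**2. How hospitals add up to the arms.** Let a, b, c and d be patients per arm from three-arm, cruciate/circular, cruciate/mesh and circular/mesh hospitals, with 1:1 blocks.

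- Cruciate: a + b + c
- Circular: a + b + d
- Mesh: a + c + d

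Equal totals of 80 give b = c = d, which includes b = 0. Each comparison with control then has a + b = 80 − b patients per arm at hospitals that randomised both arms.

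**3. Bias of the pooled contrast with no treatment effect.** Write r for the hernia risk at each hospital type. Shared hospitals cancel, leaving:

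- cruciate − circular = b·(r at cruciate/mesh − r at circular/mesh) / 80
- cruciate − mesh = b·(r at cruciate/circular − r at circular/mesh) / 80

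The documents do not give b or the risks by hospital type, so both are assumed. Risk is 30% at three-arm and cruciate/circular hospitals. The widest spread, 50% versus 25%, borrows the two incidences quoted in Statistical analysis. Rejection rates come from simulation (300,000 runs, 64 evaluable per arm, two-sided 5%).

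| b | Risk at cruciate/mesh vs circular/mesh | Cruciate − circular: bias, rejection | Cruciate − mesh: bias, rejection |
|---|---|---|---|
| 0 | any | 0, about 5% | 0, about 5% |
| 20 | 30% vs 30% | 0, about 5% | 0, about 5% |
| 20 | 35% vs 25% | 20·0.10/80 = 2.5 points, about 6% | 20·0.05/80 = 1.25 points, about 5% |
| 20 | 50% vs 25% | 20·0.25/80 = 6.25 points, about 12% | 20·0.05/80 = 1.25 points, about 5% |
| 40 (all two-arm) | 50% vs 25% | 40·0.25/80 = 12.5 points, about 32% | 40·0.05/80 = 2.5 points, about 6% |

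Swapping the 50% and 25% reverses the signs. At b = 20 the biases are then −6.25 points for cruciate − circular and 20·(0.30 − 0.50)/80 = −5 points for cruciate − mesh.

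**4. Size of the randomised comparison.** At b = 20 there are 80 − 20 = 60 enrolled and 60·0.8 = 48 evaluable per arm. Power for 30% versus 10% at 5% is Φ[(0.20·√48 − 1.109)/0.548] = Φ(0.51) ≈ 69%, against the stated 80%.

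**The case against.** The authors foresaw the problem and planned the same-centre analysis. A reader might infer that it is optional, because the sentence says it is done as judged appropriate. The natural reading is that it will be done for the primary variable and that the qualifier governs which secondary variables are chosen. So a safeguard exists, and what remains is which analysis is primary.

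The trial also limits hospital differences: the incision is measured to a set rule, the examiner comes from outside the colorectal team, and clinically negative patients have a prone CT at 12 months under a specific radiology protocol. The quoted 25% and 50% come from two separate sources and are not rates at this trial's hospitals. The 50% versus 25% rows are therefore an upper illustration. They also place the extremes where they hurt cruciate versus circular most, and the mesh comparison is barely affected in those rows.

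Other stronger readings are not supported:

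- **That equal arms of 80 require circular/mesh hospitals.** The condition b = c = d is also met when every hospital is three-arm. It forces such hospitals only if some choose two arms, blocks are 1:1 and totals are exactly equal. The protocol gives no block ratios.
- **That type I error is certainly inflated.** This depends on risk differing by the arms a hospital chose.
- **That circular/mesh patients are worthless.** They add nothing to a direct comparison with control, but a hospital-stratified model can use them indirectly.

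An SAP could add stratification by hospital. That weakens any complaint about the bare chi-square test. It does not remove the point, because the unrestricted population and the secondary status of the same-centre analysis are choices stated in the protocol.

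**Conclusion.** The point stands as a matter of which analysis is primary. As written, the primary contrast may mix randomised comparisons with comparisons between hospitals that chose different arms. This follows from the text and needs no assumption beyond some hospitals taking up the two-arm option.

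The size cannot be fixed from the documents. It is zero if no hospital is two-arm or if risk is equal everywhere, modest under a 10-point spread at b = 20, and large only if two-arm hospitals dominate and risks differ widely. The direction is also unknown. If two-arm hospitals are used with 1:1 blocks and equal totals, 80 per group overstates each randomised comparison by b per arm.

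**What to change.** 1. For each experimental-versus-control comparison, make primary the analysis restricted to hospitals that randomised both arms and stratified by hospital, for example Mantel-Haenszel. This uses the stratum already built into the randomisation. Because the choice of arms is fixed before entry, the restriction does not break the randomised comparison. The Bonferroni-Holm step is unchanged.
2. Make the pooled chi-square on the full analysis set the sensitivity analysis.
3. Track and state recruitment per randomised comparison as well as per arm, with the power those numbers give.

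The cost is a change of wording before database lock, with no new data. The downside is that fewer patients count in each comparison, so the stated power becomes less favourable. Requiring the control arm at any two-arm hospital that joins later is an optional design choice and not part of this correction.
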